### Description of all interventions and comparisons

#### Treatment details

Both the real and sham BVA groups will receive a total of six pharmacopuncture sessions over three weeks. In the BVA group, 26-gauge sterile disposable syringes (Noksipja, Seoul, Korea) containing bee venom diluted with normal saline (0.9% NaCl) will be used, whereas normal saline without bee venom with the same dose will be used in the sham BVA group. A skin hypersensitivity test will be performed on all the patients at LI 11 acupoints with subcutaneous injections of 0.05 ml of 1:20,000 bee venom preparation. Local swelling over 10 mm in diameter or redness over 20 mm in diameter will be considered positive reactions, and these patients will be excluded from this study. At the first pharmacopuncture session, all participants will receive a copy of the *Exercise Manual for Patients with Low Back Pain* from the spine center of KHUHGD and will be encouraged to exercise according to the manual during the entire treatment period. As a rescue therapy to minimize the risk of disease deterioration during the trial period, all the participants will be prescribed loxonin (Loxoprofen, 60 mg/tablet; Dong Wha Pharm Co., Ltd., Seoul, Korea) per os one tablet three times a day throughout the treatment period.

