### Data collection

A series of measurements to assess back pain-related dysfunction, pain, quality of life and adverse experiences will be collected at baseline and week 1, 2, 3, 4, 8 and 12. At the screening visit, patients will be asked to fill out a questionnaire regarding their sociodemographic characteristics, including age, gender, marital status, residence, occupation and education level. A medical history will be also taken before their physical check-ups, and these factors will determine their eligibility for our study. Participation in can be ended at any stage if the patient refuses to continue or in the presence of significant clinical deterioration, as determined by the attending KMD researchers. For those participants who will be lost to follow-up and who drop out, intention-to-treat analysis will be applied to the existing data (Table 2).

**Table 2 T2:** Schedule for data collection: outcome measures per visit

**Measures**	**Baseline (Week 0)**	**Week 1**	**Week 2**	**Week 3**	**Week 4**	**Week 8**	**Week 12**
Sociodemographic characteristics	x						
Back pain history	x						
X-ray	x						
Visual analogue scale for bothersomeness of low back pain	x	x	x	x	x	x	x
Visual analogue scale for pain intensity of low back pain	x	x	x	x	x	x	x
Oswestry Disability Index	x	x	x	x	x	x	x
EuroQol-5D	x	x	x	x	x	x	x
Beck's Depression Inventory	x	x	x	x	x	x	x
Adverse experiences^a^		x	x	x	x		x
Credibility test^b^	x			x			

a. Adverse experiences : Any adverse experiences at any visit during treatment sessions and 12 weeks will be monitored. The research team will review all trial protocols, monitor patient safety and investigate any adverse events. b. Credibility test : The credibility of the real and sham treatments will be assessed using the validated Korean version of the credibility test.

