#### Primary outcome measurements

Bothersomeness from LBP will be assessed using the 10-cm VAS for bothersomeness of LBP [18]. To evaluate the clinical severity and impact on activities of daily life in patients with CLBP, the VAS for bothersomeness is selected as a primary outcome measurement. Using the 10-cm VAS (0, absence of bothersomeness; 10, the worst bothersomeness imaginable), the patient will be asked to report the degree of bothersomeness from LBP within the past week. Bothersomeness of LBP will be measured at every single visit at baseline and 1-, 2-, 3-, 4-, 8- and 12-week follow-ups after beginning treatment. The primary end point is the third week follow-up, which marks the end of the six pharmacopuncture sessions.

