### Sample size determination

We have performed sample size calculations for CLBP according to another acupuncture study on the same disease using the same primary outcome measure because no such BVA research has been reported [28]. The expected mean difference and common standard deviation between the two groups are estimated (mean difference = 1.5, SD = 2.73) according to that former acupuncture research [28] on CLBP using the 10-cm VAS as a primary outcome measure. For two arms (control-sham BVA and experimental-BVA), we consider the two-sample *t*-test model. Twenty-seven participants will be required per intervention group to achieve 0.80 power (1-β) at the 0.05 α level after adjusting for a 20% attrition rate.

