### Data analysis

The statistical analysis will be performed in the principle of intention-to-treat analysis and per-protocol analysis. For the intention-to-treat analysis, data will be processed with the last observation carried forward method.

A homogeneity test of the baseline characteristics will be performed on both demographical and clinical data using a two-sample *t*-test for quantitative data and a chi-square test for qualitative data. The two-sample *t*-test will be used for the VAS to evaluate the bothersomeness of LBP at baseline and again at four weeks (primary endpoint) for the comparison of the two groups and to determine differences from baseline. For each outcome variable, an analysis of covariance will be performed on the data to adjust the baseline characteristics. Trends over time and time-by-treatment interactions will be explored using a repeated-measures analysis of variance. A chi-square test or a Fisher’s exact test will be performed to determine the difference between groups and the adverse effects, which will be recorded and described as frequency and percentage. All statistical analyses will be carried out with the Statistical Package for the Social Sciences (SPSS, Inc., Chicago, IL, USA) for Windows version 18.0, and a significance level of 0.05 will be used.

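### The primary endpoint is week 3 in the outcomes section but week 4 in the analysis section, so the primary test is not at the declared endpoint and the choice is left open

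*Protocol article*

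**What the plan says.** Two sections of the protocol article each label a time point as primary for the same measure.

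- **Primary outcome measurements:** "The primary end point is the third week follow-up, which marks the end of the six pharmacopuncture sessions".
- **Data analysis:** the two-sample t-test on the bothersomeness VAS is to be done at baseline and "again at four weeks (primary endpoint) for the comparison of the two groups and to determine differences from baseline".

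Three other places bear on whether these could be the same visit:

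- **Data collection:** measurements "will be collected at baseline and week 1, 2, 3, 4, 8 and 12". Table 2 gives weeks 3 and 4 separate columns and marks the bothersomeness VAS in both.
- **Primary outcome measurements:** follow-up visits are counted from the start of treatment, and the VAS asks about the preceding week.
- **Treatment details:** each arm receives "a total of six pharmacopuncture sessions over three weeks".

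On the error rate, the Data analysis section says only that "a significance level of 0.05 will be used". It gives no order of testing and no adjustment covering weeks 3 and 4.

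**The concern.** A confirmatory trial needs one primary comparison, fixed in outcome and in time. Here the outcome is fixed and the time is not. The harm has two parts.

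1. **What is estimated.** With a one-week recall, the week 3 score describes the last week of injections. The week 4 score describes the first week without them. An effect that fades quickly could appear at week 3 and not at week 4, and a delayed one could do the reverse. The two visits answer different questions.
2. **Control of the 0.05 level.** Both results will be available, and either could be reported as the prespecified primary with a citation to this article. Two chances at 0.05 do not give an overall 0.05. A reader of the final report could not tell whether the week was fixed in advance or chosen later.

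In addition, the only between-group efficacy test to which the analysis section attaches a time is not at the endpoint that the outcomes section declares.

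**Working it through.** **Step 1. Are the two statements about one visit?**

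| Place | Primary time | Reason given |
|---|---|---|
| Primary outcome measurements | Week 3 | Marks the end of the six sessions |
| Data analysis | Week 4 | None |
| Abstract | Not stated | – |
| Sample size determination | Not stated | – |

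Baseline is week 0 in Table 2, visits are counted from the start of treatment, and treatment lasts three weeks. Week 3 is therefore the end of treatment and week 4 is one week later. A different way of counting weeks does not explain the difference, because both columns exist in Table 2.

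**Step 2. Does the sample size settle it?** No. Its inputs ("mean difference = 1.5, SD = 2.73") carry no time point. The 27 per arm also does not follow from them. For two-sided 0.05 and power 0.80, n per arm = 2 × [2.73 × (1.960 + 0.842) / 1.5]² ≈ 52, and 52 / 0.8 = 65 after 20% attrition. That is a separate problem and is not used below.

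**Step 3. What does a free choice of week do to the type I error?**

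Inputs:
- Level 0.05, from Data analysis. The side is not stated; two-sided is assumed, so the critical value is 1.96.
- Two tests, week 3 and week 4, with statistics Z₃ and Z₄.
- Correlation r between Z₃ and Z₄, which equals the within-arm correlation of the two weeks' scores. The article gives none, so a range is shown.

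Formula under no effect at either week, with (Z₃, Z₄) bivariate normal:

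P(at least one significant) = 1 − P(|Z₃| ≤ 1.96 and |Z₄| ≤ 1.96)

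At r = 0 this is 1 − 0.95² = 0.0975. For other r it comes from the bivariate normal distribution function:

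| Assumed r | Either week significant, two-sided 0.05 | Either week significant in favour of bee venom (nominal 0.025) |
|---|---|---|
| 0 | 0.0975 | 0.0494 |
| 0.5 | 0.0907 | 0.0454 |
| 0.6 | 0.0875 | 0.0438 |
| 0.7 | 0.0835 | 0.0417 |
| 0.8 | 0.0781 | 0.0390 |
| 0.9 | 0.0704 | 0.0352 |
| 0.95 | 0.0646 | 0.0323 |

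A simulation with 400,000 draws, run for r from 0.5 to 0.9, agrees with the two-sided column to within 0.001. With one named week and one test, the error is 0.05 whatever r is.

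**The case against.** The contradiction itself cannot be argued away: both statements are current text. The case on the other side concerns how much follows from it.

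- **Week 3 may still be tested.** The Data analysis section also plans an analysis of covariance for every outcome and a repeated-measures analysis over time. This stands in part. It would be too strong to say that week 3 can never be tested. But the covariance analysis names no time point, and the repeated-measures analysis is exploratory, so neither makes week 3 the primary test.
- **Nobody says success may be claimed at either week.** True. The error figures describe what the text permits, not a stated plan. The Design section also says the statistical analyses are done blind to allocation. That makes it harder to steer by direction of effect, but it does not stop a choice made on the p-value.
- **The correlation may be high.** The visits are a week apart, and carrying the last observation forward gives identical values at both visits to anyone who left before week 4. That pushes r up and the error towards the low end, about 6.5% at r = 0.95. It still does not reach 5%.
- **Week 3 is not proved to be the intended time.** The outcomes section ties week 3 to the end of the sessions but gives no argument against week 4. This is fair. Week 3 is the better-supported reading, not a certainty.
- **Loxoprofen.** It is prescribed for as long as treatment lasts. If that means the three weeks of injections, week 4 also follows its end, which widens the difference between the visits. The length is not given in weeks, so the argument here rests on the injections alone.

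An unseen analysis plan could name one week, but it would still contradict one of these two sections.

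**Conclusion.** The concern holds and must be fixed. The article calls two different scheduled visits primary for one outcome, and its timed primary test is not at the endpoint it declares. The more serious consequence is that the treatment effect to be estimated is undefined: end of treatment, or one week after. The second is a type I error of about 7% to 9% instead of 5% if either week may be reported, for r between 0.9 and 0.5. It is about 6.5% at r = 0.95 and cannot exceed 9.75% for non-negative r. These figures assume two-sided tests, no effect at either week, and a claim of success at whichever week is significant. The contradiction depends on none of these assumptions.

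**What to change.** In Data analysis, change the time of the primary t-test from four weeks to three weeks, so that it agrees with Primary outcome measurements, the section that defines the endpoint and ties it to the end of the sessions. List week 4 with weeks 1, 2, 8 and 12 as secondary time points. Check the change against the protocol approved by the review board. If that document names week 4, correct the outcomes section instead, so that one week stands in both places. If both weeks are truly meant to be primary, say so and split the level, for example 0.025 each.

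Make the change by dated amendment before any unblinded data are seen, and carry it into the analysis plan. The Trial status section says recruitment is still under way, so this can be done. The cost is one line of text, with no change to visits, data or treatment. Only the option of two primary weeks has a further cost, since each test at 0.025 has less power.

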### Data handling

Investigators will enter the information required by the protocol into the case report forms. Non-obvious errors or omissions will be put into data query forms, which will be used for the researchers’ workshop. The data will be gathered and summarized with respect to demographic baseline characteristics, effectiveness and safety observations.

## Discussion

The results from this study will determine the efficacy and safety of BVA on CLBP as an adjunctive treatment to pharmacotherapy that reflects daily practice. These results can provide clinical evidence regarding whether BVA can be beneficial in pain alleviation and changing disease-related functional status.

Previous randomized clinical trials that compared the efficacy of BVA with acupuncture or normal saline injection on LBP [29,30] have been underestimated due to their poor methodological quality. In this study, participants from both the real and sham BVA groups will be treated by the same protocol to minimize the non-specific and placebo effects. All procedures (including the BVA increment protocol administered into predefined acupoints) have been rigorously designed by a process of consensus with experts and previous research according to the Standards for Reporting Interventions in Clinical Trials of Acupuncture. However, the blinding and allocation concealment could be compromised by the manifestation of a bee-venom-specific response in patients in our experimental group, including pain, swelling, redness of the skin and itching, which could be perceived by patients. We will try to blind and conceal group allocation between patients, assessors, acupuncturists and researchers by having an independent researcher prepare both real and sham BVA procedures. The results of this trial will be available in August 2013.

### Trial status

The trial is currently in the recruitment phase.

## Abbreviations

BDI: Beck’s Depression Inventory; BVA: Bee venom acupuncture; CLBP: chronic low back pain; EQ-5D: EuroQol 5-Dimension; KHUHGD: Kyung Hee University Hospital at Gangdong; KMD: Korean medical doctors; LBP: lower back pain; ODI: Oswestry Disability Index; VAS: visual analog scale.
